## 13. Outcomes

The primary outcome is the reduction of prevalence of infection of *S. haematobium* and/or *S. mansoni* from the MDA intervention at study endpoint. For purposes of sample size calculations, a 50% reduction in prevalence has been anticipated (i.e., from 20% to 10% after 12 months). As there are negligible existing studies reporting reductions in prevalence of schistosomiasis following community-based treatment, this number has been based on a drug efficacy study of PZQ syrup administered to preschool-aged children, where the reported cure rate against *S. mansoni* was 50.6% [38].

Secondary outcomes to be measured are:(i)To quantify the infection of *S. haematobium*, *S. mansoni* and STH in preschool-aged children, out-of-school children, and adults, including pregnant women;(ii)To assess reductions in intensity of infection of *S. haematobium* and/or *S. mansoni* in study sites at the final timepoint;(iii)To assess reductions in prevalence and intensity of infection of STH in study sites at the final timepoint;(iv)To assess treatment coverage at each timepoint;(v)To investigate associations between the interventions and morbidity, WASH, and demographic factors from the questionnaires; (vi)To assess access of the interventions in the study sites by participants and critical success factors for future implementation, via qualitative assessment;(vii)To investigate the cost-effectiveness of the interventions and household equity impact by detailed examination of the resource use and cost changes of delivery within the study settings.

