More precisely, the analysis of the primary outcome will be as follows: initially descriptive analysis for overall schistosomiasis (urinary or intestinal) prevalence will be presented per time. If the prevalence is more than 5%, descriptive results will also be presented by gender, age-ranges (pre-school children, school-children, adults), and community per time. Adjusted analysis taking into account the nested structure of the data: repeated measurements within study participants within households will be performed through population average logistic regression models that typically use generalized estimating equations (GEE) [41]. Such models will produce an estimate of the log(odds ratio) that compares the average prevalence of infection (averaged across all clusters: individuals within households) at each time point (i.e., time will be included as a covariate) controlling at the same time for individual—(i.e., age, gender and socioeconomic status as derived from socioeconomic variables included in the questionnaires), as well as household-level covariates [42]. Age, gender, and socioeconomic status are also likely confounders, and thus will be tested in the models. In these models, two-way interactions of time with sex, age, and communities will be considered to explore differences in prevalence rates between different groups. Missing data will be handled through multiple imputation or weighted GEE [43,44].

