For the secondary outcomes defined as reductions in prevalence of STHs, we will follow a similar approach as the one outlined above for schistosomiasis, and separately for each of the three STH parasites; we will proceed with GEE models if overall prevalence levels were estimated from the descriptive analysis to be above 5% at baseline in each of those. Subsequently, to assess reductions in the different WHO categories of intensities of schistosomiasis and STHs infections, we will employ similar reasoning for different multinomial GEE models for each of these parasites. For the baseline associations between intensities of infection and morbidity indicators, we will consider different multinomial GEE models for each of the examined parasites (i.e., schistosomiasis and STHs). For the baseline associations between prevalence of infection and WASH indicators, we will consider different logistic GEE models for each of the examined parasites (i.e., schistosomiasis and STHs). All analyses will be conducted using SAS version 9.4 for Windows (SAS Institute Inc., Cary, NC, USA). In all of the models mentioned above, the final retained explanatory variables will be based on information criteria between different fitted models (whenever those are available) and Wald tests. Spatial analysis may be employed to create visual prevalence and/or risk maps of schistosomiasis and STH in the study areas (STATA, R, and QGIS/ArcGIS). For schistosomiasis, at the household level, scatter-plots and semi-variograms will be produced to investigate the relationships between household location and proximity of the shoreline. For qualitative analyses, semi-structured interviews and focus group discussions will be analysed using the framework approach [33]. This approach allows for both deductive and inductive theme identification, through two main phases consisting of five steps:

Phase 1: Data managementStep 1: Familiarisation- the analysis team will read and re-read the verbatim transcripts to ‘familiarise’ themselves with the data and take note of key themes emerging.Step 2: Developing a thematic/coding framework through which to sort the data based on original aims and objectives, and any inductive themes identified during familiarization.Step 3: Indexing/coding data- the thematic/coding framework will be applied to all the data using NVIVO software, Microsoft Word or Excel.

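### The primary outcome is a prevalence reduction, but the only modelled estimate is an odds ratio for time, from a model whose covariates and time interactions are selected on the same data

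*Protocol article*

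**What the plan says.** **Outcome scale.** Section 13 states: "The primary outcome is the reduction of prevalence of infection of" *S. haematobium* and/or *S. mansoni* at study endpoint. For planning, "a 50% reduction in prevalence has been anticipated (i.e., from 20% to 10% after 12 months". Section 15 sizes the follow-up on those two proportions.

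**Analysis scale.** Section 14 starts with description: "initially descriptive analysis for overall schistosomiasis (urinary or intestinal) prevalence will be presented per time". If prevalence exceeds 5%, it is also shown by gender, age range and community. The adjusted analysis, which handles repeated measurements within people within households, "will be performed through population average logistic regression models that typically use generalized estimating equations (GEE"). Its result is stated: "Such models will produce an estimate of the log(odds ratio) that compares the average prevalence of infection" at each time point. Missing data are to be handled by multiple imputation or weighted GEE.

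**Covariates.** One sentence of Section 14 says the model controls for age, gender, socioeconomic status and household-level covariates. The next says: "Age, gender, and socioeconomic status are also likely confounders, and thus will be tested in the models". Interactions of time with sex, age and community are considered in the same models. A later sentence, which applies to all models described before it, says "the final retained explanatory variables will be based on information criteria between different fitted models (whenever those are available) and Wald tests".

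**The concern.** Two features of the plan combine.

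First, outcome and planning value are on the prevalence scale, while the one estimate that accounts for clustering and missing data is on the odds scale. The descriptive prevalences are on the right scale, but they are unadjusted and no interval is stated for them.

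Second, the model behind the odds ratio is not fixed. Covariates are described both as controlled for and as tested, and the retention rule covers the primary model. A logistic odds ratio is non-collapsible: the coefficient for time changes with the covariates in the model even when prevalence falls by the same amount. The population-average property of a GEE averages over clusters, not over covariates in the linear predictor. If selection keeps a time interaction, the time coefficient describes a reference subgroup, and the plan gives no way to recover the overall reduction that Section 13 asks for.

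At stake is whether the adjusted result answers the primary question directly and is defined before the data are seen.

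**Working it through.** **1. The plan's own figure.** Section 15 gives 7.85 for the squared sum of normal quantiles, p0 = 0.20 and p1 = 0.10:

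n = 7.85 × (0.20 × 0.80 + 0.10 × 0.90) / 0.10² = 7.85 × 0.25 / 0.01 = 196.25; × 1.6 (the 60% buffer) = 314.0 per site; × 3 = 942.

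This reproduces the stated size and confirms that the trial is powered on a difference in prevalence. Nothing below alters it.

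**2. The planned effect on each scale.**

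- Prevalence ratio: 0.10 / 0.20 = 0.50, a 50% reduction.
- Difference: 0.10 − 0.20 = −10 percentage points.
- Odds ratio: (0.10/0.90) / (0.20/0.80) = 0.111 / 0.25 = 0.444, which is 55.6% lower odds.

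Section 3 admits communities from 10% prevalence and states no ceiling. For a halving from other baselines:

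| Baseline → endpoint | Odds ratio | Lower odds | Gap from 50% |
|---|---|---|---|
| 10% → 5% | 0.474 | 52.6% | 2.6 points |
| 20% → 10% | 0.444 | 55.6% | 5.6 points |
| 30% → 15% | 0.412 | 58.8% | 8.8 points |
| 40% → 20% | 0.375 | 62.5% | 12.5 points |
| 50% → 25% | 0.333 | 66.7% | 16.7 points |

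**3. Dependence on the covariates kept.** Hold the overall change at exactly 20% to 10% and solve for the time odds ratio conditional on the covariates. The protocol gives no covariate effects, so all of these are assumed.

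- One balanced binary covariate with odds ratio 2, 3, 5 or 10 for infection: 0.439, 0.432, 0.421 or 0.406.
- An illustrative set built up in turn (sex, odds ratio 2; three equal age groups, 1, 4 and 2; three equal socioeconomic groups, 1, 1.5 and 2; one balanced household factor, 2): 0.444 with none, 0.439 with sex, 0.426 adding age, 0.422 adding socioeconomic status, 0.417 with all four.

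Moderate effects therefore move the estimate by about 0.02 to 0.03. Larger shifts need strong covariates.

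**4. Selecting main effects only.** A simulation took 942 people measured twice, complete follow-up, 20% to 10%, household clustering, four time-fixed covariates with assumed odds ratios of 1.2 to 1.5, cluster-robust standard errors and 1,200 replicates. Wald selection dropped about 2.2 of the 4 covariates. The mean time odds ratio was 0.440 with selection and 0.439 with all forced in, and coverage was about 94% for both. No harm from main-effect selection is visible here.

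**5. Selecting time interactions.** Three are considered: sex, age and community. The plan states no retention threshold. If each were tested at 5%, independently and with no true interaction, the chance of keeping at least one would be 1 − 0.95³ = 0.143. A simulation under assumed inputs (942 people measured twice, no true interaction) kept at least one in about 18% of runs. In those runs the time odds ratio ranged from about 0.27 to 0.65, against about 0.43 from a fixed model. These figures illustrate the mechanism and depend on the assumed inputs.

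**The case against.** The strongest case on the other side has four parts.

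- **The odds ratio is a correct and standard summary.** A value of 0.444 describes a fall from 20% to 10% exactly on the odds scale. A reader might infer that the plan overstates the reduction. It does not: that would happen only if someone read the odds ratio as a prevalence ratio, and Section 14 never says it will be presented that way. This part stands.
- **The reduction stays visible.** Raw prevalence is shown at each survey, and by subgroup if it is above 5%. This stands too, but those figures are unadjusted and come with no stated interval.
- **Selection does little harm.** A reader might infer that the intervals for time lose nominal coverage. The documents do not show this. Age group, sex and socioeconomic status change little within a person, so dropping them hardly affects a same-person contrast, and step 4 agrees. The reassurance does not extend to selected time interactions or to differential drop-out. Nor does it follow that these covariates cannot confound: 658 people per site are enrolled and 314 followed (314/658 = 48%), so composition may differ between surveys. Listing them as likely confounders is reasonable.
- **An article condenses the full plan.** Post-estimation detail could well sit in a document not shown, so its absence alone would be no finding. The retention rule, however, is stated and covers the primary model, as is the conflict between controlling for and testing the same covariates.

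**Conclusion.** The point holds in a limited form. The modelled primary estimate is on a different scale from the stated outcome, and a stated rule lets the data choose both its covariates and its time interactions. At the planned rates the scale gap is 0.444 against 0.50. Covariate choice moves the odds ratio only to about 0.42 under moderate assumed effects. The practical weakness is the interactions: if one is retained, there is no single overall time effect to report.

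The covariate effects and both simulations rest on assumed inputs. The sample size is unaffected, and so is the null hypothesis, since an odds ratio of 1 is a prevalence ratio of 1. This is a free improvement, not an error that invalidates the analysis.

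**What to change.** In Section 14, for the primary model:

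1. Pre-specify time, community, age group, sex and socioeconomic status, with no selection. Remove the conflict between controlling for these covariates and testing them.
2. Make the interactions of time with sex, age and community separate secondary analyses.
3. From the fitted GEE, report the standardised prevalence at each survey, averaged over one fixed covariate distribution. Give the endpoint-minus-baseline difference and ratio with 95% intervals clustered on household as the primary estimate, and the odds ratio as supplementary.
4. Confine selection by information criteria or Wald tests to the risk-factor models (WASH and morbidity).

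The cost is a few sentences and routine post-estimation from the model already planned. It needs no new data, visits or participants.

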## 15. Sample Size Calculation

Sample size calculations are for the primary outcome, assuming a baseline schistosomiasis prevalence of infection of 20%. Sample size calculations are calculated separately for baseline and follow-up. 

Baseline sample size: This was estimated using a hypergeometric formula (due to small overall community size):$$n=Nz^{2}\rho q/\left(E^{2}\left(N-1\right)+z^{2}\rho q\right)$$
where: *N* = population size (1500 people); *p* = estimated prevalence (0.2); *q* = 1 − *p*; *E* = accuracy of estimation (0.03); *z* = 1.96 (confidence level 95%).

A 40% buffer was applied to take into account differences in necessary covariates (including age and sex). The baseline sample size per site is 658 people per community of 1500 people. Assuming three communities, 1974 participants will need to be sampled for parasitology and questionnaires.

Follow-up sample size: It is assumed that there will be a post-intervention reduction in prevalence of 50% (i.e., from prevalence of 20% to 10%; see outcomes). This gives an assumed baseline population of 132 ‘infected’, and first-round follow-up of 66 ‘cured’. An additional 20% buffer for age and sex (10% each), and a 10% loss to follow-up between each follow-up have been added. Using a sample size formula for matched proportions:$$\;n={\left(Z_{\frac{\alpha }{2}}+Z_{\beta }\right)}^{2}\;\times \;\left[p_{0}\left(1-p_{0}\right)+p_{1}\left(1-p_{1}\right)\right]/{\left(p_{0}-p_{1}\right)}^{2}$$
where: *n* = number of individuals required; (*Z*_α/2_ + *Z*_β_)² = test statistic of 7.85, based on standard normal distribution values assuming significance of 0.05 and power of 80%; *p*_0_ = estimated prevalence at baseline (20%); *p*_1_ = estimated prevalence at follow-up (10%).

Assuming a 60% buffer, 314 participants per site will need to be longitudinally followed up each round. Therefore, for three study sites, a total of 942 subjects would be targeted to be followed up.

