## Abstract

(1) *Background:* Current international policy for schistosomiasis and soil-transmitted helminthiasis (STH) control emphasises mass administration of deworming drugs in school-based programmes. However, this approach is insufficient to control the transmission of these diseases, and their burden in non-school cohorts is recognised, albeit under-researched. This research will investigate the feasibility and acceptability of expanding access to praziquantel (PZQ) against schistosomiasis, and albendazole (ALB) against STH, to communities in selected transmission settings in Ghana. (2) *Methods:* A three-site longitudinal study will be implemented to investigate the effectiveness of expanding treatment strategies for PZQ and ALB to community members. In the context of community mass drug administration (to preschool children, school non-attending children, and adults, including pregnant women), the intervention will be assessed in a random sample of community members, at baseline with follow-up at 6, 12, and 18 months. In each community, 658 participants will be enrolled, and 314 followed up at each time point. The primary outcome measure is the prevalence of infection of *Schistosoma haematobium* and/or *S. mansoni* at study endpoint, as assessed by longitudinal surveys. Secondary outcomes are to quantify the infection of schistosomiasis and STH infections in non-treated cohorts, reductions in prevalence of STH, and intensity of schistosomiasis and STH, and treatment coverage. Nested within this study will be qualitative, cost-benefit, and cost-effectiveness evaluations that will explore accessibility, feasibility, and economic impact of expanded treatment from different complementary perspectives. (3) *Discussion:* Using a multidisciplinary approach, this study will generate evidence for improved availability, acceptability, affordability, and accessibility to deworming drugs against schistosomiasis and STH to individuals and communities in Ghana. This is likely to have considerable research, programmatic, and political value to contribute evidence for national programme policy development within Ghana, and, more broadly, World Health Organization policy development.

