## 4. Study Design

This longitudinal study will comprise baseline and follow-up surveying of the same individuals. Baseline surveying will involve screening urine and stool samples from a random selection of participants to assess infection prevalence and intensity, and conducting questionnaires to determine associations with WASH and morbidity from both schistosomiasis and STH. Qualitative focus group discussions and in-depth interviews will be held with community members and key informants to assess the understanding of the current MDA strategy, its strengths, and weaknesses, and to identify the feasibility and acceptability of expanding treatment in communities. Comparisons will be made: (i) after 6, 12, and 18 months; and, (ii) to the provision of annual MDA in the regular National School-Based Deworming Programme in schools in the same health districts, at the same time points as a means of comparison to the existing school-based deworming programme in similar prevalence settings. Drug treatment coverage for each survey will also be measured.

This study will involve expanding access to PZQ+ALB treatment for the broader population, including preschool-aged children, out-of-school school-aged children, and adults, including pregnant women. An annual community-based PZQ+ALB treatment will be provided by community health nurses and trained field staff, with cross-checking of enrolled school-aged children so as not to double-up treatments that have been provided in school-based MDA. Treatment will be provided at baseline and 12 months, and the associated reductions in prevalence and intensity of schistosomiasis and STH will be assessed (Figure 2). Parasitological examinations and questionnaires will be conducted on a random sample of participants to determine associations with morbidity from both schistosomiasis and STH, and investigate the feasibility of scale-up. An experienced and trained social science team will conduct qualitative interviews with teachers that are involved in administering annual MDA, and focus group discussions with purposively selected groups of participants by gender, age, and socio-economic status, as well as parents and caregivers.

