## 6. Individual Random Selection for Parasitological Examinations and Questionnaires

The study is an augmentation to the current standard of care (annual school-based MDA). With a longitudinal study design, random selection is only required at the individual level for parasitological and epidemiological investigations; all of the individuals in the community will be offered treatment. In each community, following sensitisation, households will be enumerated, with approximate number of residents recorded. Based on the number of households and indicative number of residents in each community, households will then be randomly selected according to a process of selecting every other (odd number houses) household to achieve the sample size. Where a household, or an individual within a household refuses, or is absent during the study, the household will be replaced by the next enumerated household. All the residents within the selected households will be requested to provide urine and stool specimens, and to complete questionnaires. At this stage, individual consent will be elicited, with age, sex, and school-attending status recorded and a unique participant identification number allocated. Selection will proceed until the minimum sample size is achieved. All community members will be invited to receive treatment, with additional consent elicitation by field staff. Treatments will be directly observed, and treatment coverage data will be recorded for all individuals.

For comparison to annual school-based MDA, a junior school (comprising children aged 6–14 years in classes 1 to junior high 3) will be selected at the time the national NTD Control Programme visit occurs. Prior to the deworming, school directors and class teachers will be asked to prepare class lists with the name, age, and sex of the children. Class lists will be imported into Microsoft Excel and each individual will be assigned a computer-generated random number. Individuals will then be selected by study investigators in ascending number order. Individuals who are not present on the day will be replaced by the next individual on the list, until the minimum sample size for parasitological testing is achieved.

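### 314 per site is built as the number entering follow-up but stated as the number followed at every round, and the follow-up cohort within the 658 enrolled is not consistently defined

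*Protocol article*

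**What the plan says.** Section 15 sizes baseline and follow-up separately. Baseline is 658 per community. For follow-up, the article assumes prevalence falls from 20% to 10%, translates this into 132 infected at baseline and 66 cured at the first follow-up, and states: "An additional 20% buffer for age and sex (10% each), and a 10% loss to follow-up between each follow-up have been added". After giving the formula, it applies a total buffer of 60% and concludes that "314 participants per site will need to be longitudinally followed up each round", or 942 over three sites.

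The abstract puts it as: "In each community, 658 participants will be enrolled, and 314 followed up at each time point". Follow-up is at 6, 12 and 18 months. Section 4 says: "This longitudinal study will comprise baseline and follow-up surveying of the same individuals".

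Section 6 describes how households are selected at enrolment, including replacement of those who refuse or are absent, and says: "Selection will proceed until the minimum sample size is achieved". The article gives no separate statement of which enrolled people make up the follow-up cohort.

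**The concern.** A sample size inflated for drop-out is a number to start with. The number expected to remain is smaller, and shrinks at each visit. Section 15 says the inflation has been made and then uses the inflated figure as a constant count at all three rounds. Both cannot be true of one closed cohort.

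The second difficulty is which cohort is meant. The infected and cured counts are computed on 658 people and the target on 314, within one paragraph. The primary outcome is a change in prevalence in the same people, analysed by GEE on repeated measurements, with multiple imputation or weighting for missing data (section 14). If 314 is a planned subsample, the other 344 per site are unobserved by design. If all 658 are to be sought, those not seen are missing and must be handled as such. The analysis and the retention rate need to know which applies. If neither is fixed, a count of 314 can be reached with the people who are easiest to find, and their infection status may differ from that of the rest.

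**Working it through.** **Inputs, all from section 15 and the abstract.** Multiplier 7.85; p0 = 0.20; p1 = 0.10; age and sex buffer 20%; loss 10% between follow-ups; total buffer 60%; 658 enrolled per site; three rounds.

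**1. Reproduce the plan's figure.**
- n = 7.85 × (0.20 × 0.80 + 0.10 × 0.90) / 0.10² = 7.85 × 0.25 / 0.01 = 196.25.
- 196.25 × 1.60 = 314.0, which matches exactly.

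**2. Where the 60% comes from.** The split is not written out. Combining the stated components:

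| Combination | Factor | n per site |
|---|---|---|
| 1.2 × 1.1³ | 1.597 | 313.5, rounded up to 314 |
| 1.2 / 0.9³ | 1.646 | 323 |
| 1.2 × 1.3 | 1.56 | 306 |
| 1 + 0.20 + 0.30 | 1.50 | 294 |
| 1.2 × 1.1² (two losses only) | 1.452 | 285 |

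The first row, a 20% covariate buffer with 10% compounded over three intervals, is the only one of these that gives 314.

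**3. If 314 enter follow-up**, with 10% lost in each interval:
- 6 months: 314 × 0.9 = 283
- 12 months: 314 × 0.9² = 254
- 18 months: 314 × 0.9³ = 229

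**4. If 314 are needed at a given round**, the number entering must be:
- for 6 months: 314 / 0.9 = 349
- for 12 months: 314 / 0.9² = 388
- for 18 months: 314 / 0.9³ = 431

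**5. If all 658 are followed**, the same losses leave 658 × 0.9 = 592, 658 × 0.9² = 533 and 658 × 0.9³ = 480. Each exceeds 314, by 278 at 6 months and by 166 at 18 months.

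**6. Infected and cured counts.**
- On 658: 0.20 × 658 = 131.6 and 0.10 × 658 = 65.8, which are the plan's 132 and 66.
- On 314: 0.20 × 314 = 62.8 and 0.10 × 314 = 31.4.
- Share of those enrolled: 314 / 658 = 47.7%, leaving 344 per site.

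**7. Does power suffer?** With the plan's own variance, power = Φ(0.10 / √(0.25/n) − 1.96). For n = 229 this is about 86%; for n = 314, about 94%. Both exceed the planned 80%.

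**The case against.** The split of the 60% is not stated, and other sums reach exactly 60%: the 40% baseline buffer plus the additional 20% for age and sex, or 20% plus four increments of 10%. This stands as far as it goes, and 1.2 × 1.1³ is a reading rather than a proof. But the 40% plus 20% route leaves no room for loss, which contradicts the statement that "a 10% loss to follow-up between each follow-up have been added". The other route still has drop-out inside 314.

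A second defence is that 314 is a minimum and everyone enrolled will be sought. Following the same individuals, and the 132 and 66, both point that way, and 658 with 10% losses keeps well above 314 throughout. The reading is possible. It sits awkwardly with an abstract that enrols 658 and follows 314, and with a stated total of 942 to be followed. If it is what was meant, a short restatement settles the matter.

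A reader might also infer that field teams will stop tracing once 314 people are found. The article does not say so: the rule of selecting until the number is reached is written for household selection at enrolment. Nor can a fall to 229 and a refill to 314 both occur; they are alternative consequences of two readings.

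Finally, a condensed article may leave the choice of a subsample to the full protocol. That answers the missing selection rule, but not the figures that the article itself states and that disagree.

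**Conclusion.** The point holds as an inconsistency in the stated numbers and in the definition of the follow-up cohort. If 314 enter, about 229 per site are expected at 18 months; if 314 are required at 18 months, about 431 must enter; if all 658 are followed, about 480 are expected. These figures assume 10% loss in each of three intervals, counting baseline to 6 months as one.

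Two stronger conclusions are not supported:
- **That the study is underpowered.** By the plan's own formula, 229 exceeds 196 and gives about 86% power per site.
- **That the result will be biased by a known amount.** Selection by availability is permitted by the wording but not prescribed. The article gives no prevalence by availability from which to size a bias. Enrolled people carry identifiers and baseline data, so those not followed could be identified and compared with those who were.

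What remains is that, as written, neither the denominator for retention nor the status of the other 344 people per site (unsampled or missing) can be determined for the primary within-person comparison.

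**What to change.** Define the follow-up cohort at baseline in one of two ways:
- all 658 enrolled per site, with about 592, 533 and 480 expected at 6, 12 and 18 months; or
- a random subsample of enrolled households, drawn and fixed before the first follow-up.

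In either case, attempt everyone on the list at every round, allow no substitution, and report retention against the list. With a subsample, say that the remaining people are baseline-only by design, so that they are not treated as missing.

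Restate section 15 and the abstract as numbers entering and numbers expected at each round, for example 314 entering and about 283, 254 and 229 remaining. Write out how the 60% is composed. Base the infected and cured counts on the same cohort: about 63 and 31 for 314, or 132 and 66 for 658.

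The subsample option costs wording and one random draw among people already enrolled. Seeking all 658 costs more follow-up visits, but keeps more information and needs no selection step.
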